### Quantitative Data Analysis

Given the complexity of the intervention, selecting a comparison group is inherently complex. To provide statistical estimates for effectiveness, we will consider three complementary approaches: (1) a within-subject controlled analysis, (2) comparison to a cohort of similar patients, and (3) a population-level analysis assessing use of healthcare services over time. While each has interpretive caveats, they provide complementary perspectives, and together provide a clearer indication of the impact of C2C.

#### Within-Subject Comparison

In a within-subject comparison, patients serve as their own controls, eliminating the need to account for confounding due to immutable patient factors. However, observed changes in use may be due to other factors such as changes in health status over time or concomitant interventions. We will use generalized linear mixed-effects models with a negative binomial distribution to examine the ED visit rate, hospitalization rate, 30-day readmission rate and cumulative hospital bed days over the two time periods (12 months before and after enrolment), adjusting for age, sex, ethnicity, and comorbidities. We will use one-way repeated measures ANOVA to assess changes in patient-reported outcomes. We will perform stratified analyses based on phase at time of enrolment and by pre-program ED visit rate.

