## Abstract

**Introduction:** Vulnerably housed individuals, especially those experiencing homelessness, have higher acute care use compared with the general population. Despite available primary care and social services, many face significant challenges accessing needed services. Connect 2 Care (C2C) is a novel transitional case management program that includes registered nurses and health navigators with complementary expertise in chronic disease management, mental health and addictions, social programs, community health, and housing, financial, transportation and legal resources. C2C bridges acute care and community services to improve care coordination.

**Methods and Analysis:** We will perform a mixed-methods evaluation of the C2C program according to the Donabedian framework of *structure, process and outcome*, to understand how program structure and process, coupled with contextual factors, influence outcomes in a novel intervention. Eligible patients are homeless or unstably housed adults with complex health conditions and high acute care use. Change in emergency department visit rate 12-months after program enrolment is the primary outcome. Secondary outcomes include 12-month post-enrolment hospital admissions, cumulative hospital days, health-related quality of life, housing status, primary care attachment and substance use. Qualitative methods will explore experiences with the C2C program from multiple perspectives and an economic evaluation will assess cost-effectiveness.

**Discussion:** Academic researchers partnered with community service providers to evaluate a novel transitional case management intervention for vulnerably housed patients with high acute-care use. The study uses mixed-methods to evaluate the Connect 2 Care program according to the Donabedian framework of structure, process and outcome, including an assessment of contextual factors that influence program success. Insights gained through this comprehensive evaluation will help refine the C2C program and inform decisions about sustainability and transferability to other settings in Canada.

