**Figure 1 F1:**
[figure not shown]
Program implementation and study timeline.

To be eligible for the program, patients must be ≥ 18 years of age, homeless or unstably housed (38), have ≥ 3 ED presentations, or ≥ 2 hospitalizations within the past year. While definitions of high acute care use vary, we chose the most conservative definition (18) in order to make the program inclusive and allow refinement to occur over the initial phases of implementation. Preliminary data gathered for the first 127 patients referred to the program before expansion indicates that, on average, C2C patients had 9 ED visits in the year prior to referral and 20% had a hospital admission. The most common reasons for admission were cellulitis, sepsis, pneumonia, substance use and other mental health diagnoses. C2C patients were more likely to be male (66%), 29% identified as Indigenous, 88% used substances and 78% were homeless. Referrals are accepted from acute care facilities, health clinics, and community agencies. Reasons for referral include attachment to primary care, housing support, connection to substance use treatment, advocacy, and discharge planning.

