#### Power Calculation

We calculated power for the within-subject comparison for the primary outcome of ED visit rate over 12 months. Under ideal conditions intensive case management with outreach may reduce ED visits by 30% in high users (18). Assuming a mean pre-intervention rate of 9.3 visits/year (as noted for Phase 1 patients) and a post-intervention rate of 6.5 visits/year, a common standard deviation of 10, and a correlation between paired observations of 0.05, a sample of 257 individuals will provide more than 90% power to detect a difference at the 5% level of significance. Note that if the correlation increases, the power will increase, hence our choice of a low correlation. We have a waiver of consent to access administrative health data; therefore all patients that engage with the C2C team are eligible for inclusion in the administrative data analysis. Given our use of administrative data with full capture for participants in Alberta, any loss to follow up will be due to outmigration or invalid personal health insurance numbers. Despite this expected attrition, with 249 engaged patients in July 2018, by end of 2019, we will have an adequate study sample to detect meaningful differences.

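### The year that qualifies patients for C2C is also the 'before' year of the only powered comparison, so its before/after change contains regression to the mean that cannot be told apart from a programme effect

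*Protocol article*

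**What the plan says.** The Abstract defines the primary outcome: "Change in emergency department visit rate 12-months after program enrolment is the primary outcome".

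The eligibility text under The Connect 2 Care Intervention requires that adults with unstable housing "have ≥ 3 ED presentations, or ≥ 2 hospitalizations within the past year".

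Under Within-Subject Comparison, each patient's 12 months before enrolment are compared with the 12 months after: "We will use generalized linear mixed-effects models with a negative binomial distribution to examine the ED visit rate". Other utilisation outcomes are modelled in the same way, with adjustment for demographic factors and comorbidity. The section warns that "observed changes in use may be due to other factors such as changes in health status over time or concomitant interventions". It then adds: "We will perform stratified analyses based on phase at time of enrolment and by pre-program ED visit rate".

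Power Calculation covers this comparison only. It takes 9.3 visits per year before and 6.5 after, an SD of 10, "a correlation between paired observations of 0.05" and 257 patients, and claims more than 90% power.

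A propensity-matched cohort and a population trend analysis are planned alongside. The Cost Analysis section uses the same pre/post contrast for health care costs.

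**The concern.** The entry rule and the baseline of the outcome use the same variable over essentially the same window. A patient whose visits happened to run high that year is more likely to qualify, and the following year will on average be lower whatever the programme does. This needs no change in health and no other intervention, only year-to-year variation and a threshold. Serving as one's own control removes fixed patient differences but not this effect. Neither a patient random effect nor the listed covariates correct for selection on the baseline count.

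The same mechanism acts within strata of pre-program ED rate. Conditioning a change on its own baseline makes the fall largest in the heaviest users even when C2C does nothing, which invites a false conclusion about whom to target. The results are meant to inform decisions on sustaining and extending the programme, and the pre/post cost comparison carries the same bias.

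**Working it through.** **1. The plan's own figure.** Inputs from Power Calculation: difference 9.3 − 6.5 = 2.8; SD 10; correlation 0.05; n = 257; two-sided 5% (sidedness is not stated).

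- SD of the difference = 10 × √(2 × 0.95) = 13.78; SE = 13.78/√257 = 0.860.
- Power = Φ(2.8/0.860 − 1.96) = 90.3%, or 90.0% with the paired t. The stated power reproduces, so the sample size arithmetic is not in question.
- Smallest significant fall = 1.96 × 0.860 = 1.69 visits, or 18% of 9.3.

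**2. Expected fall with no programme effect.** Let m be the mean in the population from which patients are selected and r the year-to-year correlation there. The document gives neither, so both are assumed. The expected post-year mean is m + r(9.3 − m), and the fall is (1 − r)(9.3 − m).

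Assume gamma-Poisson counts with shape k, selected at 3 or more visits, with k chosen so that the selected mean is 9.3. The hospitalization route is ignored. If each person's rate is perfectly stable, r = m/(k + m). If only half of the between-person variation persists, r is half of that.

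| m | k | fall, stable rates | fall, half persists |
|---|---|---|---|
| 3 | 0.277 | 0.53 (6%) | 3.42 (37%) |
| 4 | 0.419 | 0.50 (5%) | 2.90 (31%) |
| 5 | 0.611 | 0.47 (5%) | 2.38 (26%) |
| 6 | 0.889 | 0.43 (5%) | 1.86 (20%) |
| 7 | 1.343 | 0.37 (4%) | 1.34 (14%) |

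Example for m = 4: stable r = 4/4.419 = 0.905, fall = 0.095 × 5.3 = 0.50. Half persists: r = 0.453, fall = 0.547 × 5.3 = 2.90. So the range is 4-6% for stable rates and roughly 15-35% for moderate stability.

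**3. Chance of a significant result with no effect.** Φ(artefact/0.860 − 1.96), using the plan's SD, correlation and n:

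| artefact | visits | chance of p<0.05 |
|---|---|---|
| 5% | 0.465 | 8% |
| 10% | 0.93 | 19% |
| 20% | 1.86 | 58% |
| 30% | 2.79 | 90% |

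**4. Strata on pre-program ED rate.** In the same model with no effect, the post-year mean in a stratum with pre-year mean x is m + r(x − m). Here dispersion is 1/k.

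- Dispersion 1 (m = 6.30, stable r = 6.30/7.30 = 0.863): the stratum above 12 visits goes from 19.3 to 6.30 + 0.863 × 13.0 = 17.5; the 3-5 stratum goes from 3.9 to 6.30 − 0.863 × 2.4 = 4.2, a rise.
- Dispersion 2, stable rates: the 3-5 stratum goes from 3.85 to 3.91, essentially flat.
- Dispersion 3, stable rates: the 3-5 stratum goes from 3.83 to 3.79, a slight fall.

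The heaviest stratum falls most in every setting; the direction in the low stratum depends on where it lies relative to m.

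**5. Power of a controlled contrast.** Assume 257 per group and the plan's figures.

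- Adjusted for the pre-year count: residual variance 100 × (1 − 0.05²) = 99.75; SE = √(2 × 99.75/257) = 0.881; 2.8/0.881 = 3.18; power 89%.
- Difference in change scores: variance of a change 190; SE = √(2 × 190/257) = 1.216; 2.8/1.216 = 2.30; power 63%.

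**The case against.** **The plan does not say that the artefact will be reported as a programme effect.** A reader might infer this from the power statement, but no section calls the within-subject model the primary analysis. Quantitative Data Analysis presents it as one of three approaches to be read together. The caveats allow that other factors may explain a change, and the Discussion puts the lack of randomised controls first among its limitations. This stands, and it limits the point to a bias in one estimate. It does not remove the bias: the caveats describe real changes over time, whereas regression to the mean arises from selection alone.

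**Less exposed analyses are already planned.** The matched cohort addresses predictors of enrolment, and prior use is an obvious one; an article may leave the covariate list and index date to a fuller document. The population analysis applies one use threshold at every quarter, so regression to the mean does not by itself create a trend there. Both points stand. However, the cohort's stated entry rule is a housing-related code and one Calgary visit, with no use threshold, and neither analysis has a power statement.

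**The correlation of 0.05 does not show near-complete regression.** Taken literally it would, and the null fall would then be very large. In one setting (dispersion 1) the null post-year mean comes out at 6.45, close to the planned 6.5. But Power Calculation explains 0.05 as deliberately low so as not to overstate power. It is a safety margin, and the 6.45 depends on the dispersion chosen.

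**The low stratum need not rise.** Step 4 of the working shows that it can rise, stay flat or fall.

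**The magnitudes mix models.** The selected counts behind the table have an SD of 6.4 to 8.0, against the plan's 10, and the rejection rates use a paired test, not the negative binomial mixed model. They show order of magnitude only. Patients who qualify on hospitalizations alone are also selected less directly on ED visits.

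**Conclusion.** The point holds as a bias in the within-subject estimate and in its strata on pre-program ED rate. The overlap of the selection window with the baseline window follows from the protocol's own text, and nothing in the stated model removes the resulting fall.

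The size is uncertain. It is minor, about 4-6%, if individual rates are perfectly stable. If they are only moderately stable it is roughly 15-35%, a range that includes both the 18% fall that reaches significance at n=257 and the 30% planned as the programme effect. These figures rest on the assumed count distribution, the assumed source mean and persistence, and selection on ED visits alone. The direction does not depend on the exact values: with no effect, the expected change is downward whenever the selected mean exceeds the source mean and the year-to-year correlation is below 1.

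Because this is the only comparison with a power statement, the plan should settle before analysis which contrast carries the primary-outcome conclusion.

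**What to change.** 1. Rest the primary-outcome conclusion on the planned matched comparison. Require controls to meet the same use threshold at an index date. Model post-year ED visits by negative binomial regression, adjusted for the pre-year ED count, with an offset for follow-up time. This assumes that controls with the same prior count and covariates would have had the same following year; unmeasured differences remain, as the Discussion already concedes.
2. Report the within-subject result as supportive. Add a sensitivity version with months 13-24 before enrolment as baseline. That year is not used for selection and lies as far from the qualifying year as the post-year does, so in a stable process with no effect the two would have equal means. It may predate housing instability for some patients. For those enrolled in late 2015 it reaches back before 2014, the start of the window stated for the comparison cohort.
3. Report strata on pre-program ED rate only as C2C-versus-control contrasts within stratum.
4. Name regression to the mean as a main caveat, including for the pre/post cost analysis.

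The cost is analysis wording and some further administrative look-back; enrolment and eligibility are unchanged. With 257 per group on the plan's figures, power is about 89% instead of more than 90%. Adjusting for the baseline count is preferable to differencing change scores, which would give about 63%.

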#### Patient-Report Outcomes

We will collect the following patient-reported data from C2C patients at 6 and 12 months post-enrolment using in-person structured interviews comprised of closed-ended questions: health-related quality of life using the EuroQoL 5 Dimensions (EQ-5D) questionnaire (41); housing information [where they slept at night for the past 2 weeks and self-perceived stability and satisfaction (42)], primary care data (attachment [yes/no], self-perceived quality) and risk factors {drug intake [DUDIT (43)], smoking (daily/occasional/not at all), and alcohol intake [AUDIT-C (44)]}. We will also ask patients if they have achieved goals that were set at program intake and how the C2C team helped. We will obtain baseline data, including demographic characteristics, housing and income status, substance use, and patient goals from program records. In a subset of participants, we will perform a more detailed housing assessment using the Residential Time-Line Follow-Back method, to determine the number of days in a particular housing type and the number of housing transitions (38). Given the variation and complexity of the study population, we expect loss to follow-up and difficulties in collecting 6 and 12 month post-enrolment data from all engaged patients. The C2C team will utilize their strong relationships with patients and robust partnerships with community agencies and social services to retain engaged patients and locate patients for post-enrolment evaluations. In addition, C2C patients will be provided a $25 CAD VISA gift card at each instance of data collection, to compensate them for their time.

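### One-way repeated measures ANOVA is fixed for all patient-reported outcomes, although it does not suit the categorical ones and in standard form uses only patients seen at every visit

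*Protocol article*

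**What the plan says.** The section Within-Subject Comparison assigns one method to the whole set: "We will use one-way repeated measures ANOVA to assess changes in patient-reported outcomes". In the same paragraph, the administrative outcomes get negative binomial mixed models.

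The section Patient-Report Outcomes defines the set. It includes "health-related quality of life using the EuroQoL 5 Dimensions (EQ-5D) questionnaire", the DUDIT and AUDIT-C scores, where patients slept over two weeks, ratings of housing, "primary care data (attachment [yes/no], self-perceived quality") and "smoking (daily/occasional/not at all"). It adds a question on goals: "We will also ask patients if they have achieved goals that were set at program intake and how the C2C team helped".

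On timing: "We will collect the following patient-reported data from C2C patients at 6 and 12 months post-enrolment". On baseline: "We will obtain baseline data, including demographic characteristics, housing and income status, substance use, and patient goals from program records". On completeness: "we expect loss to follow-up and difficulties in collecting 6 and 12 month post-enrolment data from all engaged patients". The stated responses to loss are retention efforts by the team and its partner agencies and a gift card. The Discussion accepts that patients with more barriers may be missed.

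The Abstract lists attachment, housing and substance use among the secondary outcomes, alongside quality of life.

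**The concern.** Two features of the named method conflict with the data described.

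- **Outcome type.** ANOVA compares means under a constant-variance model. A yes/no item has a mean (a proportion), but its variance changes with that mean, and a difference from an ANOVA table is not the natural summary. A three-level smoking item has a mean only after arbitrary scores are assigned. A sleeping-place category has none.
- **Missed visits.** The classical form needs a value at every time point, so a patient who misses one interview is lost from the analysis of that outcome, including the values that were collected.

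At stake are named secondary outcomes on attachment and housing. Their estimates would be less precise than the data allow and would describe only patients who could be located each time. This is a stated choice of method, not a detail left for an analysis plan to fill in.

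**Working it through.** **The plan's own figure.** The article gives no sample size or power for the patient-reported outcomes. Its one figure, 257 individuals, is for emergency department visits. It reproduces: SD of the difference = 10 × √(2 × (1 − 0.05)) = 13.78, difference = 9.3 − 6.5 = 2.8, and a paired t-test (two-sided 5% assumed) gives power 0.9005. It does not bear on this point. Below, 257 serves only as a convenient starting count.

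**Step 1: method against outcome.**

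- EQ-5D, DUDIT, AUDIT-C: scores, so a mean-based analysis is defensible.
- Primary care attachment: yes/no by definition, so a binary model is needed.
- Smoking: three levels by definition, so an ordinal model is needed.
- Sleeping place: categorical, unless recoded as a number of nights.
- Goal achievement: asked in a way that implies yes/no.

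**Step 2: does the significance test fail on a yes/no item?** Simulation under no change used three time points, n = 50, 100 and 250, prevalence 0.1 to 0.9, and 4,000 runs per setting. Rejection at the 5% level was 0.045-0.057 with equal correlations and 0.050-0.061 with unequal correlations and no sphericity correction. The test roughly keeps its level. The fault lies in the model and the effect measure.

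**Step 3: patients retained.** The article gives no attendance rate. Assume 60% are seen at 6 months and 50% at 12 months.

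- Both visits: lowest 0.60 + 0.50 − 1 = 0.10; highest min(0.60, 0.50) = 0.50; if independent 0.60 × 0.50 = 0.30.
- At least one visit: lowest max(0.60, 0.50) = 0.60; highest min(1, 0.60 + 0.50) = 1.00; if independent 1 − 0.40 × 0.50 = 0.80.

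Other rates, starting from 257 with the same independent loss L at each visit, complete cases = 257 × (1 − L)²:

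| L | 10% | 20% | 30% | 40% | 50% |
|---|---|---|---|---|---|
| Both visits | 208 | 164 | 126 | 93 | 64 |

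If instead the same patients miss both visits, the count is 257 × (1 − L), for example 206 at 20%. The gain from using all visits then shrinks.

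**Step 4: direction of bias.** Assume true attachment of 0.30, 0.50 and 0.50 at baseline, 6 and 12 months, so the true change is 0.20 at both follow-ups. Assume also a latent correlation of 0.5 and total loss of 20% to 50%. Two assumed loss patterns:

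- *Patients unattached at 6 months are lost at twice the rate of the others.* With b = L/1.5, the completer proportion at 6 months is 0.5 × (1 − b)/(1 − L). This is 0.5 × 0.867/0.8 = 0.54 at L = 20% and 0.5 × 0.667/0.5 = 0.67 at L = 50%. Simulated completer baselines are 0.313 and 0.350, so the 6-month change is 0.541 − 0.313 = 0.23 and 0.666 − 0.350 = 0.32. The 12-month change is 0.513 − 0.313 = 0.20 and 0.556 − 0.350 = 0.21.
- *Patients unattached at baseline are lost at twice the rate of the others.* Simulated completer values give a 6-month change of 0.509 − 0.331 = 0.18 at 20% loss and 0.543 − 0.425 = 0.12 at 50%.

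The first pattern overstates the 6-month change and barely moves the 12-month change. The second understates the change.

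**The case against.** The best defence has four parts.

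- **The scores.** Several instruments yield scores for which ANOVA is an ordinary choice. This stands, and the point does not extend to them beyond missed visits.
- **The yes/no test.** A mean of 0/1 values is a proportion, and the test keeps its level in Step 2. This stands too. A reader might call the analysis invalid, but that is too strong: it is a poorly suited model and summary.
- **Missing data.** The article states no completers-only rule, and missing-data handling is usually specified in a fuller document. That is partly right. Restriction to complete cases follows from the named method in its standard form and is not written down. But the method itself is written down, for every outcome, beside a statement that loss is expected.
- **Size of the loss.** A reader might infer heavy loss. The article says only that loss is expected, gives no rate, and describes retention measures.

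Two further inferences are tempting. One is that, with interviews only at 6 and 12 months, the ANOVA collapses to a paired t-test. The baseline list names housing and substance use from program records, so three time points are plausible for those. EQ-5D, smoking and attachment are not named there, but the list is not exhaustive. The other is that completers must overstate benefit. In a within-patient comparison, a more stable group may differ in level without differing in change, and Step 4 shows that the error can run either way.

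Finally, the gain from using all visits should not be oversold. A patient with one follow-up and no baseline value gives no direct within-patient change.

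**Conclusion.** The point holds in a limited form. The method named for all patient-reported outcomes does not suit attachment, smoking or, unless recoded, sleeping place. In standard form it also discards patients with any missed visit although missed visits are foreseen. Under the assumed 60% and 50% attendance, 10-50% of patients would have both visits and 60-100% at least one; under independence, 30% against 80%. These figures rest wholly on assumed rates. Selection of easier-to-locate patients is a reasonable worry, but its direction and size are not established.

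The outcomes concerned are secondary. The primary analysis of emergency department visits uses administrative data and a count model, so nothing here weakens it. The change should be made because it is cheap and brings these outcomes into line with the approach already used for the administrative ones.

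**What to change.** Replace the ANOVA sentence with models named by outcome type:

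- linear mixed models for EQ-5D, DUDIT and AUDIT-C scores;
- logistic GEE or logistic mixed models for attachment and other binary items;
- ordinal or multinomial models for smoking and housing category.

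State that every available visit is used, including baseline where it was recorded, and say for which outcomes a baseline value exists.

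Add a sensitivity analysis for missing interviews. One option is response weights built from program records and linked administrative use. Linkage will fail for patients who leave the province or have invalid health numbers, so the weights apply where it succeeds. Neither mixed models nor such weights remove bias if data are missing not at random, and the text should say so.

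The cost is a few sentences of analysis wording and modest programming, with no new data.

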### Measures of Effectiveness

#### Acute Care Use

We will use administrative health data to assess acute care use among C2C patients 12-months before and after enrolment: ED visits (primary outcome); hospital admissions; repeat ED visits within 72 h of discharge; unplanned readmissions within 30 days among hospitalized patients; total hospital bed days; deaths; ED and hospital discharge diagnoses; and ICU admissions. Data will be obtained by linking unique provincial health insurance numbers to administrative health data housed by Alberta Health Services.

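### Stratifying the before/after ED comparison by pre-program ED rate builds regression to the mean into the strata, so they cannot show who benefits

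*Protocol article*

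**What the plan says.** Under Acute Care Use, the primary data serve "to assess acute care use among C2C patients 12-months before and after enrolment: ED visits (primary outcome"). Under Within-Subject Comparison, negative binomial mixed models compare the ED rate "over the two time periods (12 months before and after enrolment), adjusting for age, sex, ethnicity, and comorbidities". The same paragraph closes with: "We will perform stratified analyses based on phase at time of enrolment and by pre-program ED visit rate".

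Under Power Calculation, the inputs are a pre-enrolment mean of 9.3 visits/year, a post-enrolment mean of 6.5, and "a common standard deviation of 10, and a correlation between paired observations of 0.05". The article explains the last value: "Note that if the correlation increases, the power will increase, hence our choice of a low correlation".

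Entry (The Connect 2 Care Intervention) requires at least 3 ED presentations or at least 2 hospitalizations in the past year. The Comparison Cohort section describes propensity matching but no strata by prior ED use. Regression to the mean is not named anywhere in the article.

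**The concern.** A patient's count in one year is partly a stable level and partly chance. Sorting patients on the first year's count and then examining second year minus first puts chance-high years in the top stratum and chance-low years in the bottom one. The next year moves both back towards the mean whatever the program does. The result is false effect modification, which can arise even when the overall before/after test is sound. Adjustment for age, sex, ethnicity and comorbidities does not remove it, and no choice of cut points avoids it.

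The article says its results will help refine the program and inform sustainability and transfer. A table in which the highest users gain most would be easy to read as saying whom C2C helps.

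**Working it through.** **1. The article's own figure.** SD of the paired difference = 10 × √(2 × (1 − 0.05)) = 13.78. Power = Φ(2.8 × √257 / 13.78 − 1.96) = Φ(1.30) = 0.903, and 90% power needs 255 patients. The statement "a sample of 257 individuals will provide more than 90% power to detect a difference at the 5% level of significance" reproduces with a two-sided test, so these inputs are used below.

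**2. Expected change with no effect.** With equal means and SDs in both years, expected post = 9.3 + ρ × (pre − 9.3). At ρ = 0.05, a patient with 20 prior visits is expected to have 9.3 + 0.05 × 10.7 = 9.8, and one with 4 is expected to have 9.3 − 0.05 × 5.3 = 9.0. At ρ = 0.7 the figures are 16.8 and 5.6.

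**3. Above-median stratum, no effect, no entry floor.** Counts are gamma-Poisson with mean 9.3 and SD 10. The median split is an assumption, because the article gives no cut points. The stratum's pre mean is 16.55. The last column is the share of simulated 257-patient trials with a significant fall in this stratum, using paired t tests as a stand-in for the planned mixed model.

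| ρ | Expected post | Post/pre | False fall significant |
|---|---|---|---|
| 0.05 | 9.3 + 0.05 × 7.25 = 9.66 | 0.58 | over 99% |
| 0.3 | 11.48 | 0.69 | 99% |
| 0.5 | 12.93 | 0.78 | 93% |
| 0.7 | 14.38 | 0.87 | 75% |

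The difference between strata was significant in at least 99% of trials at every ρ. The unstratified test rejected in about 5%, as it should.

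**4. With the entry floor.** Entry was simulated as at least 3 ED visits (the hospitalization route was ignored), with no effect and a median split among entrants. The background mean and SD are assumptions, and ρ is the correlation before selection. Cells give post/pre in high users, then low users.

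| Background mean, SD | Observed pre mean | ρ 0.05 | ρ 0.3 | ρ 0.5 | ρ 0.7 |
|---|---|---|---|---|---|
| 9.3, 10 | 12.4 | 0.50, 1.63 | 0.63, 1.47 | 0.74, 1.33 | 0.84, 1.20 |
| 6, 8 | 10.4 | 0.38, 1.19 | 0.55, 1.14 | 0.68, 1.10 | 0.81, 1.06 |
| 4, 7 | 9.9 | 0.29, 0.88 | 0.48, 0.91 | 0.63, 0.94 | 0.78, 0.96 |

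High users fall in every cell and look better than low users. The direction in low users changes with the background mean. Only in an extreme model (background mean 0.14 visits/year) did the two strata move by about the same amount.

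**5. Same true effect in everyone.** A uniform 30% reduction multiplies each ratio by 0.7. At background mean 9.3 and ρ = 0.5 the strata show 0.52 and 0.93, although the true ratio is 0.70 in both.

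**6. An earlier window as stratifier.** Strata taken from months 13–24 before enrolment look like an obvious remedy. Under the entry floor with no effect, they give high and low ratios of 0.96 and 0.75 (background mean 9.3, ρ = 0.5) and 0.93 and 0.57 (background mean 6, ρ = 0.5). Patients with low earlier use who still met the floor entered at a peak, so they fall most. The false gradient remains, mostly in the opposite direction.

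**The case against.** The strongest objection is that the correlation of 0.05 is not a belief about these patients. The article chose it low to be conservative for power, so it cannot be read as saying that 95% of a stratum's distance from the mean will vanish. That stands, and it is why the size is given as a range. The spurious fall is smaller at 0.7 but still present.

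A reader might also infer that the analysis will show harm in low users. The article does not support this. Everyone enters through a floor on recent acute care use, so low users too are selected upward and may appear to improve. The direction turns on a background mean that is not stated.

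Further points on the other side:
- The look-back window for the pre-program rate is not spelled out. The same 12 months is the natural reading, but the full plan may define it otherwise.
- The article gives no purpose for these strata, so narrowing the program to high users is a possible misuse and not a stated intention.
- The article concedes interpretive caveats, concomitant interventions and natural changes in health. These soften the point, but none is the mechanism described here, and none supplies a control for the strata.
- The rejection rates rest on a median split and t tests. The expected ratios do not depend on the test used.

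**Conclusion.** The point holds for the within-subject analysis stratified by pre-program ED rate. With no program effect, above-median users show post/pre ratios of about 0.6 to 0.9 for correlations of 0.05 to 0.7 (mean 9.3, SD 10, median split). Larger falls are possible once the entry floor is modelled. High users look better than low users in all but extreme settings, so the gap between strata cannot be read as effect modification. No claim is made about the direction of change in low users.

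This is a secondary analysis. The unstratified primary test and the strata by phase are untouched by this mechanism. Whether the entry floor itself biases the overall before/after change is a separate question. The conclusion assumes that the pre-program rate means the 12 months used as the before period.

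**What to change.** State that within-subject change by pre-program ED rate will not be reported as evidence of who benefits. In the planned comparison-cohort analysis:

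1. Apply the same entry criterion to controls.
2. Match on the 12-month pre-period ED count as well as the propensity score.
3. Report the C2C-versus-control follow-up ED rate ratio within pre-period ED strata, with a test of interaction.

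Regression to the mean then acts on both arms within a stratum. It cancels to the extent that matched controls share the same underlying rate. Strata from months 13–24 should not be used as the remedy, for the reason shown in step 6.

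The cost is a short change to the analysis text, using a cohort and linked data already planned. The downside is lower precision within strata and reliance on the matched controls, with the unmeasured confounding that the Discussion already concedes.
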